## Abstract

**Background:**

Physical, mental and cognitive impairments are known severe adverse outcomes in critically ill patients who have beenadmitted to an intensive care unit (ICU). Early rehabilitation interventions such as lighter sedation and increased mobilization have improved patient outcomes, but evidence for early cognitive rehabilitation is sparse.

**Aim:**

The study aims to describe the experiences of ICU survivors and their families regarding early cognitive stimulation as part of rehabilitation during and after ICU admission.

**Design:**

Our study has a qualitative, descriptive design using individual and dyad interviews as well as focus groups with ICU survivors and their families.

**Methods:**

Eligible participants are adult ICU survivors and families who are able to recall events during and after the ICU stay. We will use purposeful sampling in the outpatient clinic in the Department of Intensive Care at the Copenhagen University Hospital. We plan to conduct five individual patient interviews, four dyad interviews with patients and families, and two focus groups with patients. All interviews will follow a semi‐structured interview guide based on the study objectives and input from a patient and public involvement (PPI) panel. We will use the framework method for analysis and invite the PPI panel to participate in the analysis process to strengthen the findings. Written informed consent will be obtained from all participants, and data will be anonymized before analyses.

**Relevance for Clinical Practice:**

This study protocol provides a methodological framework to understand early cognitive rehabilitation from the perspectives of ICU survivors and their families. This study protocol presents one of the first studies to investigate the concept of early cognitive rehabilitation during critical illness from this perspective. The findings will facilitate a tailored approach to early rehabilitation to be investigated in further studies.

What is known about the topic
Many intensive care survivors experience long‐term cognitive impairment.Early intensive care rehabilitation is often driven by physiotherapists.
What this paper adds
How intensive care unit (ICU) survivors and their families experience early cognitive rehabilitation.Barriers to early cognitive rehabilitation according to ICU survivors and their families.

## INTRODUCTION

1

The number of patients admitted to the intensive care unit (ICU) and surviving critical illness is on the rise, with about 75% alive 30 days after discharge.^1^ This trend is expected to continue as the elderly population grows and medical treatments advance.

Critical illness is a condition of one or more organ dysfunctions caused by, for example, septic shock, trauma or respiratory failure requiring close monitoring and specialized care in the ICU. Patients in the ICU receive interdisciplinary intensive care from a team of health care professionals.

With the decreasing mortality rates in the ICU, there has been a shift from preventing death to preventing long‐term physical and psychological issues and promoting long‐term recovery and well‐being in ICU survivors. Physical, mental and cognitive impairments are collectively known as post‐intensive care syndrome (PICS).^2^ Cognitive health refers to the health of the brain, whereas mental health is the psychological or emotional health. Long‐term cognitive impairment affects up to 60% of ICU survivors and can be as severe as Alzheimer's disease, posing a growing public health care challenge.^3^, ^4^

Cognitive impairment in ICU survivors is linked to increased dependence on health care and family support, rendering even basic daily activities of living a challenge. Potential modifiable risk factors for long‐term impairment in the ICU include mechanical ventilation, sepsis, sedation and length of ICU stay regardless of cognitive function prior to critical illness.^5^, ^6^, ^7^ However, no gold standard exists for measuring and quantifying cognitive function in ICU survivors and cognitive decline is under‐recognized by intensivists and rehabilitation professionals.^8^

## BACKGROUND

2

Early mobilization, delirium prevention, daily breathing trials and wake‐up calls, sleep protocols and family engagement have been suggested as potential interventions and early rehabilitation strategies for the prevention of cognitive impairment, but the evidence is sparse.^9^, ^10^ A scoping review identified mobilization, physical rehabilitation and activities of daily living as the most commonly reported occupational therapist (OT) supported interventions to prevent cognitive impairment in the ICU.^11^ A recent feasibility randomized clinical trial (RCT) demonstrated that cognitive stimulation, upper limb training and activities of daily living initiated by the OT were feasible during the ICU stay.^12^ A non‐blinded RCT demonstrated that extensive cognitive follow‐up and training after ICU discharge can improve cognition and expedite the recovery period.^13^ Early cognitive rehabilitation in the ICU has been described not only as a cognitive stimulation task but also as an OT task such as activities of daily living interventions, for example brushing teeth, wiping the face, washing the body, dressing or eating dependent on cognition (arousal, attention, executive functioning), physical strength and physiological restrictions.^13^

Today, physical therapy assisted by physiotherapists is common in daily early rehabilitation, but occupational therapy assisted by OTs is not very well implemented in many ICUs.^11^ The evidence regarding nurse‐led interventions directed towards early cognitive stimulation in ICU patients is limited. In addition, the patient and family experience of early cognitive rehabilitation is sparse.

## AIM

3

The study aims to describe the experiences of ICU survivors and their families regarding early cognitive stimulation as part of rehabilitation during and after ICU admission. This study will inform the development of a nurse‐led cognitive stimulation intervention. The development will be guided by the Medical Research Council (MRC) framework for developing and evaluating complex interventions.^14^ This study is supported by a comprehensive integrative review. The protocol for this is published elsewhere.^15^

### Research question

3.1

The specific objectives of the study are:To describe the ICU survivor and family experiences of early rehabilitation in and after the ICU, and to understand the implications for recovery.To investigate facilitators and barriers to early rehabilitation in and after ICU according to ICU survivors and families.

## DESIGN AND METHOD

4

### Study design

4.1

The study has a qualitative descriptive design triangulating interview methods with ICU survivors and their families.

### Study site and setting

4.2

The study will be conducted at the Copenhagen University Hospital, Rigshospitalet, Denmark. The hospital is a national referral hospital with 1244 beds and five ICUs: thoracic, neurological, cardiac, neonatal and mixed medical/surgical ICU with a total of 60 ICU beds. The 20‐bed mixed medical/surgical ICU will host the study. Early physical rehabilitation is facilitated by an ICU physiotherapist in collaboration with an ICU nurse and physician. Patients are mobilized to a sitting position in bed or a chair as soon as their condition allows it. Routine occupational therapy is not offered.

### Participants

4.3

The participants in this study are ICU survivors and their family caregivers. Participants will be purposively sampled at the hosting department. Eligible participants are adult ICU survivors and family that are able to recollect their time in or after the ICU. We wish to obtain a maximum variation sample with different personal and socio‐economic backgrounds, as well as a range of medical conditions, in order to include different perspectives on the potential advantages of early rehabilitation in the ICU (Table 1). Inclusion and exclusion criteria are presented in Table 2.

**TABLE 1 nicc13254-tbl-0001:** Sampling of eligible participants.

Characteristics	Patient	Family
Age		
Younger (18–50 years)		
Middle age (51–75 years)		
Older (>75 years)		
Sex		
Men		
Women		
Ethnicities		
Describe if participants consent^a^		
Admission type		
Medical		
Surgical		
ICU length of stay		
Less than 7 days		
7 days or more		
Time from ICU discharge		
Less than 3 months		
More than 3 months		

^a^
Not commonly performed in Denmark.

**TABLE 2 nicc13254-tbl-0002:** Inclusion and exclusion criteria.

Inclusion criteria	Adult ICU survivor (aged ≥18 years) with at least one ICU admission
	Acute critical illness
	Family caregiver (aged ≥18 years) present during the ICU admission
Exclusion criteria	Admission due to suicide attempt
	If written consent cannot be obtained

Eligible participants will be approached by a member of the research team at the outpatient clinic, peer‐support group meetings or when in contact during other studies. The research team will inform the aftercare providers about the study. The research team will not have access to potential participants' health records, but the aftercare providers may use the patient records to identify eligible participants according to the study criteria.

The aftercare providers will give study information to eligible participants. If a patient or family member agrees to participate, their name, telephone number or email will be given to the research team. The research team will then contact the eligible participants and verbally inform them about the study and obtain verbal consent.

Written informed consent will be obtained from all participants before the interview is conducted. The consent form will be sent by email, or a paper version can be sent by regular mail at the request of the participants. The participants will be asked to complete the consent form and return it to the research team prior to the interview. At the time of the interview, the consent will be reconfirmed verbally.

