### Data analysis

4.6

Data will be analysed using the seven‐step framework method suggested by Gale et al.^23^ Step 1: All interviews will be transcribed verbatim. Step 2: The researchers will familiarize themselves with the data material by reading reflective notes and listening to audio recordings. Step 3: At least two researchers will deductively code the first transcripts using an a priori defined analytical framework (Table 3) but also be aware of other phenomena. Step 4: The researchers will compare codes and refine the analytic framework or matrix with input from the PPI panel. Step 5: The analytic framework will be applied to the rest of the data. This is an iterative process, and researchers will go back and forth in the process to add new categories to the framework if needed. Step 6: Data will be charted into the framework and condensed. Step 7: Interpretation of data: Researchers will explore linkages, connections and relationships in the data. Alongside this process, researchers will write analytic memos, noting down impressions and ideas to be shared with other researchers.^23^ Qualitative data management software, NVivo QRS version 14.23.1.38 (QRS International Pty Ltd., Doncaster, Victoria, Australia), will be used to support data analysis.

**TABLE 3 nicc13254-tbl-0003:** Framework matrix for data analysis.

	Cognitive rehabilitation	Functional rehabilitation	Other rehabilitation
Rehabilitation in the ICU described by patient			
Rehabilitation post‐ICU described by patient			
Rehabilitation needs not met			
Rehabilitation needs met by patient			
Rehabilitation needs met by family caregiver			
Rehabilitation in the ICU described by family caregiver			
Rehabilitation post‐ICU described by family caregiver			

*Note*: If other nodes need to be included in the matrix, this can be carried out and will be described during the analyses in the dissemination of the findings.

To decrease the potential for researcher bias and strengthen the findings and implications for clinical practice, the research team will meet with the PPI panel to integrate their views into the analysis process.

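### Every recruitment route in section 4.3 depends on existing clinic, peer-support or research contact, and Table 1 does not vary or record that contact, so barriers after the ICU may be under-represented

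*Protocol article*

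**What the plan says.** The second objective in section 3.1 is "To investigate facilitators and barriers to early rehabilitation in and after ICU according to ICU survivors and families". It therefore has two halves, one inside the ICU and one after discharge.

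Section 4.3 (Participants) says that eligible people will be "approached by a member of the research team at the outpatient clinic, peer‐support group meetings or when in contact during other studies". Aftercare providers support this in two ways: "the aftercare providers may use the patient records to identify eligible participants according to the study criteria", and "The aftercare providers will give study information to eligible participants". The research team itself has no access to health records.

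The same section states the sampling goal: "We wish to obtain a maximum variation sample with different personal and socio‐economic backgrounds, as well as a range of medical conditions". Table 1 lists age, sex, ethnicity, admission type, ICU length of stay and time from ICU discharge. Table 2 has two exclusions, one headed "Admission due to suicide attempt" and the other being that written consent cannot be obtained. Neither table mentions follow-up attendance, recruitment route or participation in another study.

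The framework matrix (Table 3, section 4.6) has rows for post-ICU rehabilitation as described by patient and by caregiver, and a row "Rehabilitation needs not met". Section 7 names recruitment bias as a limitation but gives no mechanism and no countermeasure.

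The abstract's Methods paragraph describes a narrower source: "We will use purposeful sampling in the outpatient clinic in the Department of Intensive Care at the Copenhagen University Hospital".

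**The concern.** For the post-discharge half of the second objective, contact with a follow-up clinic or support group belongs to the experience under study. A survivor who never reached such a service may have met the very barriers that the objective asks about. If recruitment runs through those services and through other research, the people most likely to describe failed access are the least likely to be invited. This goes beyond ordinary volunteer bias, because the selection acts on part of the topic itself.

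The stated safeguard is maximum variation, but the grid meant to deliver it omits the one dimension along which the routes narrow the sample. Because that dimension is not recorded either, neither the analysts nor a later reader could tell how far the narrowing went. The findings are meant to feed the development of a nurse-led intervention (sections 3 and 5), so a one-sided account of post-ICU barriers would carry forward into that work.

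A secondary matter is that survivors met through other studies are neither excluded nor flagged. If any of those studies delivered rehabilitation or follow-up, nothing recorded would show which accounts came from it.

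**Working it through.** This is a qualitative descriptive study sized by information power. It has no alpha, power or effect size and no stated total to reproduce. The check is a comparison of sections plus one headcount.

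**1. What each route presupposes (section 4.3)**

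| Route or channel | Prior contact needed | Stated aim of reaching non-attenders? |
|---|---|---|
| Outpatient clinic | Clinic attendance | No |
| Peer-support meetings | Group attendance | No |
| Contact during other studies | Research contact, not necessarily aftercare | No |
| Record use by aftercare providers | None stated; limited by the study criteria | No |

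The three places of approach all need existing contact. Record use could in principle reach someone without it, but the article does not say that it will be used that way.

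**2. Does the sampling grid compensate?** Table 1 has six characteristics: age, sex, ethnicity, admission type, length of stay and time from discharge. None is follow-up contact. Time from discharge is not a substitute, since a survivor more than three months out may or may not have attended anything.

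**3. Which half of the objective is exposed?** Barriers inside the ICU arose before any recruitment contact, so selection on later contact affects them less. Barriers after discharge overlap directly with the selection.

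**4. Headcount (section 4.4)**

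- Patients: 5 individual + 4 in dyads + 2 × 4 to 2 × 6 in focus groups = 5 + 4 + 8 = 17, up to 5 + 4 + 12 = 21.
- Family caregivers: 4, giving 17 + 4 = 21 to 21 + 4 = 25 participants.
- Sessions: 5 + 4 + 2 = 11.
- Individual or dyad places for patients: 5 + 4 = 9.

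Following the plan exactly, the number of the 17 to 21 patients who must be non-attenders is 0. That describes what the plan permits. It is not an estimate of bias, and the article gives no attendance rate from which to make one.

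**5. Abstract against section 4.3.** The abstract gives one source, the clinic; section 4.3 gives three. The two should agree, but the difference looks like abbreviation and changes nothing in the argument.

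**The case against.** The case against has real force on several points.

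- *Non-attenders are not barred.* Contact through another study need not involve aftercare. Aftercare providers may also search records against criteria that do not require clinic attendance. This stands. A reader might infer that survivors without aftercare cannot enter at all, and the article does not support that. It supports only that no route is directed at them.
- *Attending is not the same as having overcome barriers.* Coming to a clinic or group does not show that rehabilitation was received, and the article does not say that either one delivers it. Attenders can report unmet needs, Table 3 has a row for these, and dyads add a caregiver's view. This also stands. It would be wrong to describe the sample as people who overcame the barriers, or as people with more support than usual, since nothing says how common attendance is.
- *Rehabilitation from other studies.* A reader might infer that it would be charted as usual care. The article does not describe the other studies, and Table 3 has no usual-care category. Its note also allows extra nodes. The point is therefore only a possibility, which one recorded item would make visible.
- *The limitation is disclosed.* Section 7 names recruitment bias and section 8 calls the findings context-specific. This is true, but a general acknowledgement does not say who is missed, and it changes nothing in the sampling.
- *Any unlisted characteristic could be called missing from a grid.* That is fair in general. Follow-up contact differs because it overlaps with the post-discharge half of the second objective and because the routes themselves select on it.

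**Conclusion.** The concern holds in a limited form. The described routes all rest on existing contact with the clinic, a support group or another study; none is aimed at survivors without follow-up contact; and the grid that should secure variation neither varies nor records it. Barriers to rehabilitation after the ICU may be under-represented as a result. Findings on rehabilitation inside the ICU are less exposed.

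No magnitude can be given beyond the headcount. The conclusion assumes that survivors without follow-up contact would, at least in part, describe different post-discharge barriers from those who attend. That is plausible but is not shown in the article. It also takes section 4.3 as the full account of how participants are reached.

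The change is worth making before recruitment closes, because it is cheap and bears directly on one of the two objectives. The mismatch with the abstract is clerical.

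**What to change.** 1. Add a line to Table 1, *attended aftercare or peer support (yes/no)*, and use it as a sampling dimension. Within the same 17 to 21 patients, seek a few non-attenders for the 9 individual or dyad places. The aftercare providers would identify and invite them through the record use that section 4.3 already permits.
2. Record for each participant the recruitment route and whether they took part in another study, so that any rehabilitation or follow-up delivered by a study can be recognised when the data are charted.
3. If non-attenders cannot be reached, say so, and limit the post-ICU conclusions to survivors in contact with services or research. State this mechanism in section 7 in place of the general mention of recruitment bias.
4. Align the abstract with the routes in section 4.3.

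Cost: one more sampling line, two recorded items and a few extra invitations sent by the aftercare providers. Non-attenders may respond less often, so recruitment could be slightly slower. No additional participants or interviews are needed.

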### Sample size

4.4

We wish to conduct five individual patient interviews, four dyad interviews with one patient and one family caregiver, and two focus group interviews with four to six patients. We will use the concept of information power to estimate the sample size.^16^ We have a narrow aim, dense specificity, strong dialogue, and cross‐case analysis, which helps determine the sample size.^16^

### Data collection

4.5

We will conduct individual interviews with ICU survivors, dyad interviews with survivors and families, and focus groups with ICU survivors. The individual interviews will allow an in‐depth exploration of the participants' experiences, perceptions, and emotions regarding early rehabilitation.^17^ The dyad interviews will offer insight into the interpersonal dynamics and shared perspectives of the survivor and a family caregiver who was present in the ICU. These perspectives and experiences might reveal areas of consensus or disagreement, contributing to a more nuanced understanding of early rehabilitation. We will apply comparative analysis and investigation of how these dynamics interact.^18^ The focus groups will provide insight into how individuals construct meaning collectively by discussing early rehabilitation interventions and practices. The interaction between participants might lead to diverse perspectives, opinions, and experiences, where new ideas are fostered by group dynamic exploration of early rehabilitation.^19^

Individual and dyad interviews will be conducted either at the participants' homes or at the hospital. If a participants has any restrictions imposed by COVID‐19 or other contagious diseases, we may shift to online interviews. The focus groups will meet in a room in the hospital away from ICU.

All interviews will be conducted by the same researcher ([name]), who has experience in conducting qualitative interviews and focus group interviews. The researcher will be accompanied by a research assistant ([name]) who will observe and take notes during interviews. Additional support and training will be available from the research team as required.

Interviews will be semi‐structured, using an interview guide based on the study objectives and input from a patient and public involvement (PPI) panel. The interview guide includes time and space for the participants to recall and construct their own understanding of early cognitive rehabilitation. During the interviews, the interview guide may be adjusted as needed in response to the evolving research process. The initial interview guides can be found in the Data S1, and the final version will be made available when the results are presented.

The individual interviews are scheduled to last approximately 40–60 min. The dyad interviews are scheduled to last approximately 60–80 min and the focus groups approximately 60 min.

Interviews will be audio‐recorded, and the audio files will be saved on an encrypted and logged drive at the hospital server. Field notes made by the research assistant, including any additional comments or reflections, will be scanned and saved on the encrypted server with the audio files. At dissemination, the field notes will be anonymized. The audio files will be transcribed, and all identifiers will be removed and stored at the same location as the audio files and field notes. Audio recordings and all data will be deleted before 1 January 2027.

The COREQ (Consolidated criteria for Reporting Qualitative research) Checklist^20^ will be used when writing the manuscript for the qualitative study.

By triangulation of the three methods, the data generated might capture broader experiences and perspectives of rehabilitation of ICU survivors with potential memory loss or difficulty recalling what actually happened in the ICU.^21^, ^22^

